**Fig 1 fig1:**
[figure not shown]
Study flowchart.

### Outcome measurements

#### Primary outcomes

The primary study outcome is the incidence of anaesthesia cases with critical events (definitions in Table 1) associated with airway management requiring tracheal intubation, from the start of anaesthesia until the discharge of the patient from the PACU or end of anaesthesia (defined as handover to the paediatric or neonatal intensive care unit, the ward, or discharge home straight from anaesthesia care) in children aged 0–16 yr.

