**Methods:**

CRICKET involves paediatric patients aged 0–16 yr, requiring tracheal intubation, performed by the anaesthesia team for procedures or interventions requiring general anaesthesia, either planned or unplanned. Patient characteristics and airway management techniques are recorded using a dedicated electronic case report form. If one or more critical events associated with airway management occur, a second, more detailed questionnaire will be completed for the follow-up until the patient is discharged or up to a maximum of 30 days. We aim to include 105 000 patients from participating centres disseminated worldwide. Every participating centre collects data over a consecutive observational period of 3 months. The primary outcome is the incidence of critical events associated with tracheal intubation in children.

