## Methods

The primary aim is to determine the incidence of paediatric patients presenting with critical events associated with tracheal intubation. Table 1 presents definitions of critical events used in this study. As an observational study, CRICKET remains inherently susceptible to confounding by indication, although its large sample size and detailed, standardised data collection will help to characterise and mitigate this potential bias. Analysis of these events will focus on identifying clusters of events and risk factors for frequently occurring events. For example, in some conditions, critical events might be characterised by two or more airway-related complications occurring in close temporal proximity during the same intubation episode, suggesting a connected cascade (such as desaturation followed by bradycardia and hypotension) rather than isolated, unrelated events. Similarly, clusters of particular events might be identified in a specific subgroup of patients. This may allow us to identify independent risk factors and, consequently, children at particular risk for critical events.

**Table 1 tbl1:** Definition of critical events associated with tracheal intubation. CPAP, continuous positive airway pressure.

Definition of tracheal intubation-associated critical events	
‘Critical events’ in this study and time frame	Any episode of occurrence during tracheal intubation requiring a medical intervention from the start of anaesthesia until the end of anaesthesia (defined as handover to either the PACU, the paediatric or neonatal intensive care unit, the ward, or discharge home straight from anaesthesia care).
Severe hypoxemia	SpO_2_ <85% or >20 points below initial value for at least 60 s.
Severe bradycardia	Persistent bradycardia for at least 1 min: • 0–3 months old: HR <80 beats min^−1^ • 4 months–2 yr: HR <60 beats min^−1^ • 2–10 yr old: HR <40 beats min^−1^ • 10–16 yr old: HR <30 beats min^−1^
Oesophageal intubation	Tracheal tube placed in the oesophagus diagnosed by (video-) laryngoscopy, absence of sustained EtCO_2_ trace, absence of lung ventilation (auscultation or absence of chest excursions) causing a decrease in oxygenation.

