### Study design

CRICKET is a prospective, international, multicentre observational study collecting health-related data over a consecutive 3-month period. Centre recruitment will be sequential between January 2024 and December 2025, with each site initiating its observation window upon ethics approval and confirmation of adequate local resources. During the study period, designated research staff or the anaesthetist in charge of the patient will complete a dedicated case report form (CRF) for every child undergoing general anaesthesia with tracheal intubation, whether elective or unplanned. Importantly, CRF data are collected exclusively for research purposes and are entirely separate from the medical record. For cases without critical events, data collection ends at anaesthesia completion and tracheal extubation. When one or more critical events occur, an additional detailed section of the CRF and a structured 24-h follow-up will be completed to document management and possible sequelae. To minimise reporting bias and alleviate concerns about disclosure, data are recorded anonymously, no identifiable staff information is collected, participating centres are not benchmarked against each other, and the study explicitly adopts a quality-improvement-oriented framework to encourage accurate and complete reporting. Any missing data will be actively queried by the local study team to ensure completeness, and variables that remain unresolved after these efforts will be handled using predefined statistical procedures appropriate for observational datasets, including sensitivity analyses and multiple imputations to assess the impact of missingness.

The collected health-related data will be entered into an electronic research database in REDCap® (Vanderbilt University Medical Center, [name]) (Research Electronic Data Capture)^10^, ^11^, ^12^, ^13^, ^14^, ^15^ (see Data Management section). In this database, data will be encoded to ensure that neither patients nor providers are identifiable. The study flowchart is presented in Figure 1.

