#### Secondary outcomes

Secondary study outcome parameters are the incidences of the critical events associated with tracheal intubation and the number of critical events per case, if multiple occurred during the same case. Risk factors of critical events will also be identified.

Children with critical events associated with tracheal intubation will be followed up until complete resolution of the event or for a maximum of 30 days whichever comes earlier.

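### The primary outcome has two incompatible end points for children who go to the PACU: arrival there in Table 1, departure in the outcome statement

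*Protocol article*

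**What the plan says.** All references are to the protocol article.

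- **Table 1 (Methods)** gives the time frame of a critical event as "from the start of anaesthesia until the end of anaesthesia (defined as handover to either the PACU", followed by intensive care, the ward or home. Handover to the PACU is one of the listed ends.
- **Primary outcomes** defines the outcome as the "incidence of anaesthesia cases with critical events (definitions in Table 1) associated with airway management requiring tracheal intubation", and runs it "from the start of anaesthesia until the discharge of the patient from the PACU or end of anaesthesia". The definition of end of anaesthesia that follows lists intensive care, ward and home, but not the PACU.
- **Study design** states: "For cases without critical events, data collection ends at anaesthesia completion and tracheal extubation".
- **Follow-up after an event** is worded three ways: "follow-up until the patient is discharged or up to a maximum of 30 days" (Abstract, Methods), "a structured 24-h follow-up will be completed to document management and possible sequelae" (Study design) and "followed up until complete resolution of the event or for a maximum of 30 days whichever comes earlier" (Secondary outcomes).

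**The concern.** The study exists to estimate one incidence, so the rule that decides which cases enter the numerator has to be unique. Here it is not. A child whose first qualifying event occurs in the PACU is a case under the outcome statement and not a case under the table that the statement cites.

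The interval in dispute matters. One listed event, stridor after extubation, follows removal of the tube by definition and can begin in the PACU. Laryngospasm and hypoxaemia can also begin there.

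Two further questions follow. The first is whether the data cover the longer window at all, given where collection ends for event-free cases. The second is that, under the outcome statement, observation time depends on where the child goes next: through the whole PACU stay for some, only to handover for those going to intensive care or the ward.

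**Working it through.** **Step 1. The stated ends, side by side.**

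| Child goes to | Table 1 window ends | Primary outcomes window ends |
|---|---|---|
| PACU | handover to the PACU | discharge from the PACU |
| Intensive care, ward | handover | handover |
| Home | discharge home | discharge home |

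The two agree except for PACU patients, where they differ by the full PACU stay. The outcome statement also leaves the PACU out of its handover list, so the two texts treat the PACU differently in two respects. Loose phrasing does not explain this.

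**Step 2. Collection against each window.** For event-free cases, collection ends when anaesthesia is complete and the child is extubated.

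- Against discharge from the PACU, this is earlier for a child extubated before the PACU. The stated collection does not clearly cover a first event during the PACU stay.
- Against handover, the order is not fixed. Table 1 equates the end of anaesthesia with handover, so the two may be the same moment. For a child who leaves still intubated, extubation may come later.

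**Step 3. The plan's precision, reproduced.** The inputs come from Sample size calculation and Table 2: Wilson 95% interval, incidence p, half-width r × p. I took the smallest n for which

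z/(1 + z²/n) × √[p(1 − p)/n + z²/(4n²)] ≤ r × p.

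- p = 0.5%, r = 8.5%: n = 105 992, against 105 897 stated.
- p = 1%, r = 8.5%: n = 52 727, against 52 714 stated.

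All eight cells of Table 2 agree within 0.1%. The sample size does not depend on the window wording. It serves here only as a yardstick.

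**Step 4. How large a PACU share would matter.** Let I be the incidence under the longer window, and s the share of event cases whose qualifying events all begin in the PACU. The outcome counts cases, so a child who also had an event before handover stays in either numerator. Then

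- incidence under the Table 1 window = I × (1 − s);
- shift = I × s;
- planned half-width = r × I.

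The shift exceeds the half-width when s > r, whatever the value of I.

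| Precision taken as yardstick | Half-width relative to I | Share s above which the shift is larger |
|---|---|---|
| Chosen scenario (0.5%, Table 2) | 8.5% | 8.5% |
| Stated target, 0.9–1.1% around 1% | 0.1/1.0 = 10% | 10% |
| Projected 50 000 cases, I = 1% | 8.7% | 8.7% |
| Projected 50 000 cases, I = 0.5% | 12.4% | 12.4% |

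In absolute terms, the chosen scenario has a half-width of 0.085 × 0.5% = 0.0425 percentage points.

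The article gives no value for s. For illustration only, at I = 1% a share of 2–5% shifts the estimate by 0.02–0.05 points, and a share of 10–20% by 0.1–0.2 points. The first range lies below the 0.1-point target half-width; the second reaches or exceeds it. The document does not favour either.

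**The case against.** The strongest reply is that centres work from a full protocol and a CRF, neither shown, and that the Clinical Event Committee adjudicates every reported event against the study definitions. A reader should therefore not infer that centres have in fact counted different events. That stands. It does not settle which window the committee applies, since the definitions and the outcome statement disagree. The committee also sees only reported events.

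Four stronger readings are tempting, and the article does not support them.

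- *Collection stops before even the Table 1 window closes.* As Step 2 shows, this is certain only against discharge from the PACU.
- *A PACU event has no way into the CRF.* The sentence in Study design concerns cases without events, and a child with a PACU event is arguably not one. The section on data quality also has research staff, where available, check the previous 24 h of cases and return queries to the clinician. That route is limited, because the treating anaesthesia provider must document the event and staff may not infer it from the record alone. The supportable statement is that coverage is unclear.
- *The destination-dependent window biases the age and ASA comparisons.* This would require destination to vary with age or ASA class. That is plausible, but the article gives no figures, and a window tied to the anaesthesia team's care could be deliberate.
- *Follow-up has three incompatible lengths.* Two versions share the 30-day maximum and differ in the earlier stopping event, discharge or resolution. The 24-h follow-up may be an assessment within the longer one, though the article does not say so. No sequelae endpoint is named, so no pooled analysis is put at risk.

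**Conclusion.** The contradiction between Table 1 and Primary outcomes is real, and nothing else in the article resolves it. It concerns the sole primary numerator, so one window has to be fixed before the database is locked. If the longer window is meant, collection as described may miss first events in the PACU, and the incidence would then be too low.

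The size is unknown. At the chosen precision, a PACU-only share above about 8.5% of event cases would outweigh the half-width. This difference in definition does not shrink with more patients. The comparison assumes that s is counted in cases and that precision is expressed relative to the longer-window incidence.

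Whether the unequal window by destination distorts the age or ASA comparisons cannot be judged from the article. The follow-up wording is a minor point and does not touch the primary numerator.

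**What to change.** Before database lock, reconcile Table 1, Study design and Primary outcomes to one primary window, chosen to match what the CRF collected for every case and not after seeing the events.

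- If PACU stays were not systematically observed, end the window at handover for all destinations. Report PACU-onset events as a separate secondary count among PACU patients.
- Report the incidence under the other window as a sensitivity analysis where onset time or location was recorded.
- As a minor correction, state one follow-up rule in the Abstract, Study design and Secondary outcomes, and say whether the 24-h follow-up is an assessment within the longer follow-up.

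The cost is not wording alone. With the handover window, PACU-onset events, including some post-extubation stridor, leave the primary count. Separating events by window needs onset time or location, which the article does not say was recorded. Sites may have to be queried where it is missing, during the cleaning already planned once recruitment stops at the end of 2025.

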#### Secondary outcomes

Secondary study outcome parameters are the incidences of the critical events associated with tracheal intubation and the number of critical events per case, if multiple occurred during the same case. Risk factors of critical events will also be identified.

Children with critical events associated with tracheal intubation will be followed up until complete resolution of the event or for a maximum of 30 days whichever comes earlier.

### Study population and eligibility criteria

Patients are eligible if they fit the following inclusion criteria:•All paediatric patients, aged 0–16 yr, requiring tracheal intubation, either planned or unplanned, performed by the anaesthesia team for procedures or interventions requiring general anaesthesia.•Cases in which a surgeon performs the intubation, whether electively or as a rescue, will be included. Likewise, patients who already have an airway in place (e.g. tracheostomy or tracheal tube) and subsequently undergo airway removal followed by a new intubation will also be captured.

Exclusion criteria are as follows:•Patients >16 yr.•Patients admitted to the operating room already intubated and not requiring a tube exchange.•Refusal to give consent or withdrawal of consent if such is required by the relevant ethics committee.

### Study sites and recruitment procedures

We aim to recruit both academic and non-academic anaesthesia departments worldwide, including dedicated children’s hospitals and centres with mixed paediatric and adult practice across all continents, in order to capture a broad range of paediatric airway management approaches. The study was announced at international anaesthesia meetings and through a dedicated website (https://cricketstudy.eu/), with an open call for participating centres. Each participating institution is required to submit the protocol for approval to its local ethics committee.

Given the multinational nature of the study, requirements for informed consent will follow local ethics committee determinations, including the use of waivers where permissible. To address the potential for selection bias introduced by differing consent pathways, a planned sensitivity analysis will compare centres using prospective individual consent with those operating under a waiver or alternative approval model.

## Results

The CRICKET study is currently ongoing. In May 2025, around 25 000 patients were entered into the database, with a projected 50 000 patients by the end of 2025. Due to the observational nature of the study and the extensive international involvement and effort, the steering committee decided to stop recruiting at the end of 2025 and proceed with database cleaning, subsequent statistical analysis, and publication.

## Discussion

### Assessments of outcomes for data quality

For every patient, the anaesthesia provider will complete an electronic questionnaire in REDCap®, together with an expanded form whenever a critical event related to tracheal intubation occurs. Because complications may arise at any time during anaesthesia, treating clinicians act as an extension of the study team and are responsible for real-time, case-specific data entry; however, these study forms remain entirely separate from the clinical record. To ensure completeness and minimise reporting bias, dedicated research staff, when available and not involved in clinical care, will perform daily checks of all cases from the preceding 24 h, reviewing submitted questionnaires for clarity and retrieving missing information. Where clarification is needed, queries may be returned to the individual clinician who performed the case, ideally close to end of the case and without collecting any identifiable information. Study personnel will not infer the occurrence of a critical event solely from the medical record: an event must be affirmatively documented by the treating anaesthesia provider. Conversely, the independent Clinical Event Committee (CEC) will adjudicate all reported events, ensuring consistency with study definitions and assigning severity levels; however, the CEC cannot overrule a clinician’s explicit confirmation that an event occurred, although it may reclassify the event type or severity based on the protocol definitions. Data quality verification will take place only after all ancillary datasets are merged into the main REDCap® database. Once all outstanding queries are resolved and data quality procedures completed, the database will be locked for statistical analysis.

### Causal model for identifying determinants of critical events

Recent cross-sectional studies have suggested a relationship between the risk of critical events in paediatric tracheal intubation and patient anthropometric characteristics, anatomical variations in the airway, the presence of comorbidities, and the skill and experience of the healthcare provider. Despite these findings, no study has investigated the causal relationship between these events and the factors underlying their occurrence. Identifying and understanding the determinants of critical events during paediatric tracheal intubation are crucial for recognising and managing them effectively, thereby enhancing the quality and safety of tracheal intubation and improving the outcomes of young patients.

To estimate causal effects, we must appropriately identify, select, and include all relevant confounding variables.^10^ We will construct a directed acyclic graph (DAG) to visually represent the causal structure of our research question.^11^ A DAG provides a non-parametric depiction of cause–effect relationships and enables us to identify variables that may plausibly confound the association between exposure and outcome.^12^^,^^13^ This approach offers an intuitive visual framework grounded in rigorous causal inference methodology.^14^^,^^15^ In the CRICKET observational study, we will develop a causal model to identify factors associated with critical events during paediatric tracheal intubation. We will use a DAG to identify potential confounders that influence the relationship between critical events and their determinants. We will draw on expert opinion to define known causal pathways and exposures. We will also perform sensitivity analyses to evaluate the influence of unmeasured confounding on our findings. We will construct the DAG using the R package [CRAN (open source), Radboud University & Medical BioSciences, Nijmegen, The Netherlands (Textor)] *dagitty*,^15^ based on the web-based DAGitty platform. To minimise bias in interpreting the results, we will develop the causal model and identify the exposures of interest in parallel with the principal statistical analysis, once recruitment is complete and data cleaning has been finalised.

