### Statistical analysis

A descriptive analysis of the data will be carried out, using counts and percentages to summarise categorical data and median (interquartile range) to summarise continuous data.

The incidence of critical events will be estimated and reported together with a 95% confidence interval. Furthermore, critical event incidence will be provided for different age categories, operator’s experience, operator’s speciality, and centre volume.

In terms of risk factor analysis, a univariable and multivariable mixed-effect logistic regression model will be computed based on possible predictors, which include for example age (≤12 months), weight (≤10 kg), number of attempts (more than two), presence of comorbidities (ASA score ≥3), comorbidity related to airway management (e.g. relevant syndromes), expected difficult intubation, type of anaesthesia induction (i.v. or inhalation), no neuromuscular blocking agent given, airway surgery or ears, nose, throat (ENT) surgery, and experience level of the person performing tracheal intubation. Appendix 1 lists the relevant factors used for primary and secondary analyses. Goodness-of-fit, calibration, discriminatory capacity, and predictive skill of the regression models will be assessed using Nagelkerke pseudo-*R*^2^, calibration belts, area under the receiver operating characteristic curve (AUROC), and Brier Score, respectively.

The target sample size for CRICKET is informed by statistical considerations and the practical constraints of conducting a large, multinational observational study. Although the sample size calculation indicates that approximately 105 000 cases are required to estimate an event rate of 0.5–1% with acceptable precision, the achievable enrolment also depends on centre capacity, case volume, and the coordinated activation of participating sites across multiple jurisdictions. Recruitment will therefore proceed sequentially from January 2024 to December 2025, with each centre contributing a consecutive 3-month sampling window once local approvals and resources are in place. If the required sample size is not reached by the end of 2025, the steering committee may extend the recruitment period or, alternatively, close enrolment and proceed with analysis of the accrued data, depending on the number of events captured and the resources remaining.

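### The causal diagram and its exposures are to be chosen alongside the main analysis, with nothing stated that keeps those choosing them from the results

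*Protocol article*

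**What the plan says.** The section on the causal model (Protocol article, Causal model for identifying determinants of critical events) gives the DAG a definite job: "We will use a DAG to identify potential confounders that influence the relationship between critical events and their determinants". It names the source of the diagram: "We will draw on expert opinion to define known causal pathways and exposures". It then sets the timing: "we will develop the causal model and identify the exposures of interest in parallel with the principal statistical analysis, once recruitment is complete". The same sentence places the work after cleaning ("once recruitment is complete and data cleaning has been finalised") and gives the reason for this order: "To minimise bias in interpreting the results".

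The Statistical analysis section describes the regressions that would run over the same period. These are univariable and multivariable mixed-effect logistic models of critical events on a set of predictors, and they are introduced with wording that leaves the set open ("will be computed based on possible predictors, which include for example age"). That section refers to Appendix 1 for the factors used.

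**The concern.** A DAG restrains analyst choice only if it is settled before anyone knows which associations are strong and how they move with adjustment. Once those are known, an arrow can be added or dropped, or an exposure promoted, for reasons that owe something to the results, even without intent. A reader of the final paper could not tell whether that had occurred.

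The estimates are meant to be used. The causal section argues that no earlier study has examined causal relationships for these events. The Publication and dissemination policy expects the results to support changes in clinical strategy and training. Effect estimates whose adjustment sets were open while results were appearing would carry less weight for that purpose.

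**Working it through.** No formula applies, because the point concerns the order of two activities. The check is whether anything in the article fixes the causal model before the results, or shields it from them.

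1. **Order of events.** The Results section has recruitment ending at the close of 2025, followed by database cleaning, analysis and publication. The section on data quality says that after queries are resolved "the database will be locked for statistical analysis". The causal section starts the DAG and the choice of exposures after cleaning and runs them beside the main analysis. On these statements, the exposure–outcome regressions and the causal model are produced in the same period.

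2. **What the DAG needs.** By the article's own account its content is expert knowledge of known pathways. Neither that nor the naming of exposures needs outcome data, so nothing in the task requires waiting for the cleaned database.

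3. **What the choice can change.** The example predictors in the Statistical analysis section include both an anticipated difficult intubation and a count of more than two attempts. As an illustration, attempts may plausibly lie on the path from difficulty to a critical event. Whether the DAG treats them as a mediator or as a confounder changes what the effect of difficulty means and how large it is. That kind of decision is left open while results emerge.

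4. **Possible safeguards.**
   - *Expert opinion.* This limits free choice, but the article does not say that the experts are blind to the regressions or separate from the analysts.
   - *Sensitivity analyses.* The article promises these: "We will also perform sensitivity analyses to evaluate the influence of unmeasured confounding on our findings". They address variables that were not measured, not a result-driven choice among variables that were.
   - *Database lock.* Lock precedes analysis, but no DAG, exposure list or adjustment set is tied to it.
   - *Predictor list.* The list in the text is given by way of example. Appendix 1 is not shown; it is described as listing factors for the analyses, not as a DAG or as adjustment sets. Even if it closes the regression list, the causal section still leaves the causal exposures to be identified later.

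None of the four closes the gap.

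5. **What is untouched.** The primary outcome is the incidence of cases with critical events. The secondary incidences and the number of events per case are also descriptive. None of these depends on a DAG.

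**The case against.** The best defence has three parts.

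- **Two separate workstreams.** Running in parallel may mean a group that builds the DAG from clinical knowledge and never uses the regression output, which would fit the stated aim. The wording allows this. It does not state it, and a single clause would have done so.
- **Expert opinion as the source.** A reader might infer that the DAG will be derived from the data, so that the causal claims are already post hoc. The article does not support that. It names experts as the source and never says that the diagram will be built from, or revised in the light of, observed associations. This part stands: influence from the results is possible, not shown.
- **Detail that belongs elsewhere.** Exposure lists and adjustment sets are commonly held in an analysis plan, which is not shown here, and Appendix 1 may fix the regression factors. That would answer a complaint about missing detail. It does not answer this point, because the article itself sets the timing. An analysis plan that fixed the exposures before analysis would contradict the article's sentence.

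**Conclusion.** The point holds in a limited form. The stated schedule leaves a route by which exposures and adjustment sets for the causal analysis could be shaped by exposure–outcome results, and no blinding or separation is stated to close it. This works against the purpose given for the schedule. It is worth correcting, but it does not threaten the study's main result, because the incidence estimates are unaffected.

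The size cannot be quantified from the document, which gives neither the number of causal exposures nor the candidate adjustment sets. A reader might try to size it from the ten example predictors, as 1 − 0.95^10 = 0.40, the chance of at least one p<0.05 among ten independent null tests. That figure should not be used. It measures multiplicity and would be the same if every exposure and adjustment set had been fixed in advance. It also assumes that the ten predictors are the causal exposures, that they are independent (age up to 12 months and weight up to 10 kg clearly overlap) and that none has an effect. The article states none of these, and it reports earlier evidence of associations with patient, airway and provider factors.

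A reader might also conclude that the DAG must precede database lock. The argument does not need that: the DAG has to precede sight of exposure–outcome results, not lock as such.

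The verdict rests on the article alone and assumes that Appendix 1 does not contain a fixed DAG with its adjustment sets.

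**What to change.** Replace the timing sentence in the causal-model section with:

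> The DAG, the exposures of interest and the minimal sufficient adjustment set for each will be defined from expert opinion, finalised and dated before any exposure-outcome analysis is run or seen; later changes will be reported as exploratory.

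No new data or analyses are needed. The cost is bringing forward expert work that is already planned. The cleaning period between the end of recruitment and the analysis is a natural place for it.
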